The goal of this study is to determine the sequelae of prediction error (both amount and type) during exposures on clinical outcomes in CBT for social anxiety disorder (SAD). This disorder is characterized by excessive fear and avoidance of social situations (57). CBT for SAD presents a good case for exploring exposure prediction error effects for several reasons. First, SAD is one of the most common anxiety disorders (58), meaning recruitment may be easier and any results will be pertinent to many therapists and patients. Second, CBT is widely used and efficacious for SAD (59). Third, evidence-based CBT treatments have exposure as a core treatment component in the form of a systematic approach toward feared social situations (60–64). Finally, at the time of study design, prediction error had not been studied explicitly in CBT for SAD. Our study has three aims:

(1) The primary aim of the current study is to explore whether threat prediction error experienced during exposures in and between sessions is related to session-by-session symptom changes. We will model the effects of threat prediction and outcomes separately rather than using difference scores while isolating within-person from between-person effects, with the former being of primary interest. We will sample both in-session and homework exposures in treatment by using smart-phone based ecological momentary assessment (EMA) and generate rich descriptive information about patient exposure experiences. We hypothesize that prediction errors will be common in treatment and that negative threat prediction error during exposures between sessions will predict symptom reduction between sessions. We hypothesize that positive prediction error during exposures between sessions will predict symptom increase between sessions.

(2) A secondary aim of the current study is to explore whether the average magnitude of prediction errors experienced during treatment is associated with treatment outcome. We hypothesize that patients who experienced a greater mean level of negative prediction error across all exposures in treatment will report fewer symptoms at the end of treatment and after 3 months.

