## Methods and analysis

### Design

This longitudinal and observational study will be embedded in a larger project evaluating predictors and moderators of symptom change in adults receiving individual CBT for SAD. This treatment includes graded exposure-based behavioral experiments conducted in sessions and for homework. Assessments will be made at baseline, before each session, mid-treatment, post-treatment, and 3-month follow-up and only those relevant to the current study will be described (see Table 1). Exposure processes are the predictors of interest for this study and will be measured using event-contingent EMA of all exposures completed during treatment.

**TABLE 1 T1:** Study assessment schedule.

Measure	Assessment point															
	B	1	2	3	4	5	6	M	7	8	9	10	11	12	P	3M
SIPS	X*	X	X	X	X	X	X	X*	X	X	X	X	X	X	X*	X*
STATM	X	X	X	X	X	X	X	X	X	X	X	X	X	X	X	X
EPQ																
In-session						X	S		V	X	X					
Event contingent																

B, Baseline; 1–12, Sessions 1–12; M, Mid treatment; P, Post treatment; 3M, 3 month follow up. SIPS, Social interaction phobia scale; STATM, Social threat appraisal tracking measure; EPQ, Exposure process questionnaire; S, Safety behavior experiment version; V, Video review experiment version. *SIPS extracted Social Interaction Anxiety Scale and Social Phobia Scale in the parent study.

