#### Exposure interventions

Exposure is a central feature of the planned intervention. Participants develop one or more hierarchies of feared/avoided social situations and are then supported to systematically approach these while dropping subtle avoidance and anxiety-driven coping strategies called *“safety behaviors.”* These exposures are framed as behavioral experiments with a threat prediction testing rationale rather than a habituation rationale. Exposures begin from session 5 and are set for homework until the end of treatment. In session 5, the participant and therapist develop one or more graded hierarchies of feared social situations (depending on the needs of the participant) to work through in treatment. Participants are encouraged to do exposures from their hierarchies for homework from session 5 onward.

All exposures are determined collaboratively by the therapist and participant within the constraint that it targets the participant’s social threat cognition and associated social situation. Exposures will thus differ for each participant since they are determined based on individual needs. Examples of possible exposures include initiating conversation, talking in group conversations, dating, being assertive, talking to authority figures, eating in public, public speaking, dancing in public, or talking on the phone. The number of exposures completed for homework will likely vary for each participant, depending for example on participant motivation and compliance. Since the study will operate in pandemic conditions, homework exposures will adhere to any social distancing or lockdown regulations at the time.

In-session exposures that are guided by the therapist occur in sessions 5, 6, 7, 8, and 9. The session 5 exposure aims to introduce doing exposure using smartphone EMA while providing an early positive experience. Therapists and participants can choose the specific social activity, but the manual recommends choosing one that can be practical to complete in-session, relevant to the participant, achievable for the participant, but also that elicits anxiety. Examples could include giving a short speech or having a short social interaction. This could be with the therapist, people in the clinic, or people in short walking distance from the clinic.

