### Outcomes

The primary outcome will be self-reported social anxiety severity as measured using the 14-item Social Interaction Phobia Scale (SIPS) (73). The SIPS was reduced from the longer SIAS (74) and SPS (74). The SIPS retains good psychometric properties whilst reducing participant burden and is suitable for session-by-session symptom tracking (73). The SIPS will be administered at 16 time points including before treatment, at each session, mid-treatment (between sessions 6 and 7), post-treatment, and 3 months after treatment.

Threat prediction error is thought to trigger extinction learning and correction of inflated threat appraisal (social threat in the case of social anxiety) (22, 36). Social threat appraisals will be the secondary outcome and will be measured 16 times on the same schedule as the primary outcome. Social threat appraisals will be measured using an instrument adapted by the first author for the purpose of this study named the Social Threat Appraisal Tracking Measure (STATM). The STATM was adapted from a similar measure developed by Gregory and colleagues (75) to briefly measure and track session-by-session changes in social threat appraisals during CBT treatment for SAD. Participants read two hypothetical social tasks involving public speaking and social interaction, respectively. For each task, they are asked if they would have any fears about attempting these tasks today. If yes, they are instructed to write down their feared outcomes in an open-ended format. Then, participants rate their anxiety, perceived likelihood of feared outcome, and perceived cost of their feared outcome if they were to attempt the task today, using slider scales anchored at 0 (*Not at all*) and 100 (*Extremely*). The mean of likelihood and cost ratings across both social tasks (i.e., four items) estimates the overall degree to which the participant views social situations as threatening at that time. Higher scores indicate a greater perception of social threat. If a participant says that they would not have any fears about attempting a task that day, their score will be coded as 0. To make score comparisons meaningful, the hypothetical social tasks in the measure remain the same over repeat administrations.

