### Ecological momentary assessment procedure and measures

Prior to session five, a researcher will help each participant setup their smartphone to complete event-contingent EMA surveys *via* Qualtrics (76). Participants place re-usable hyperlinks on their smartphone home page for the duration of the study, which they can click on to initiate a survey in their web-browser. Participants also receive a user guide for their reference. Participants complete their first survey and exposure during session 5, guided by their therapist. For the remainder of treatment, therapists assign exposures for homework with verbal and written instructions for participants to complete a smartphone survey for each one. Therapists guide participants to complete surveys for additional in-session exposures during sessions 6, 7, 8, and 9.

We developed the EMA questionnaire for the purpose of this study, which we call the exposure process questionnaire. We designed the questionnaire to be clinically useful while still assessing variables of interest. It is an expanded digital version of the typical static pen-paper (or pdf) exposure record commonly used in CBT. The expanded items were mostly adapted from existing validated measures. The questionnaire has a pre- and post-experiment section and uses conditional branching to display relevant questions based on participants’ responses. Item response types include open-ended text fields, slider ratings, single-choice questions, and multiple-choice questions.

There are three versions of the exposure process questionnaire that share a core set of items (see Supplementary material for full description). The standard exposure process questionnaire (EPQ) is used for all in-session and homework exposures except for the safety behaviors exposure in session 6 and video review exposure in session 7. The EPQ assesses anxiety, threat predictions, threat outcomes, surprise, safety behavior use, learning outcome, and contextual features of the exposure (described in more detail below).

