### Analysis

The relationship between exposure processes and outcome variables over time will be explored using univariate multilevel modeling (MLM). This modeling framework has a range of strengths for our purposes. It can account for data dependencies typical in longitudinal designs, can handle assessment schedules that are unevenly spaced, and can handle unbalanced data (88). Prediction error is the exposure process of interest. We operationalize prediction error as the discrepancy between threat prediction (P) and threat outcome (O) scores for an exposure.

Prediction error effects can only be explored if enough cases of prediction error exist in the data. We will explore how many cases of prediction error and what type are present in the data before modeling. For descriptive purposes, we will categorize a prediction error as an exposure where the standardized P and O scores differ by more than 0.5 standard deviation in either direction (89). We will proceed with modeling prediction error effects if more than 10% of exposures meet the above prediction error criteria (49).

The primary aim of the study is to explore how prediction error during exposures relates to session-by-session symptom change. Exposures may occur from sessions 5 to 12. The outcomes are measured once at each session, but the number of exposures completed may vary significantly over treatment. We will aggregate EMA data obtained between sessions (e.g., between sessions 5 and 6, or 6 and 7, etc.) to form seven time points. Symptoms at time *t* will be regressed onto the mean P and mean O in the preceding inter-session interval (i.e., between *t* – 1 and *t*). We will control for the effect of symptoms at the preceding session (*t* – 1) and other theoretically relevant exposure mechanisms, specifically mean fear activation (operationalized as mean peak anxiety minus mean pre anxiety) and mean within-exposure habituation (operationalized as mean peak anxiety minus mean end anxiety) in the preceding inter-session interval. Operationalizing fear activation and habituation in these ways is consistent with most prior research, but we acknowledge the limitations of these indices noted by Bonito et al. (38) and will discuss the results in light of these.

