The secondary aim of the study is whether the average prediction error experienced during treatment predicts treatment outcome. We hypothesize that participants who experienced greater symptom improvements from baseline to 3-month follow-up will have experienced greater overall threat prediction error in their exposures during treatment. For each participant, we will calculate their mean P and O experienced across all exposures in treatment (termed txP and txO, respectively). The outcome will be symptoms at 16 time points from baseline to 3-month follow-up. We will examine the interaction of assessment point with txP and the interaction of assessment point with txO on the outcome. The hypothesis would be supported if both interactions were significant, and txO is positive in sign and txP is negative in sign. The secondary hypotheses will be exploratory because cross-level interactions likely require larger sample sizes to be adequately powered to detect a medium effect size (92).

The tertiary aim of the study is to explore whether prediction error relates to surprise and learning outcomes. We hypothesize that the larger prediction error (regardless of type) will predict larger feelings of surprise after an exposure and greater likelihood for participants to report a learning outcome. We will use the EMA data without aggregation to perform multi-level RSA with surprise as the outcome and P and O and their higher order terms as predictors. Response surface parameters will be examined to determine whether the hypothesis is supported (49, 50, 53).

We will test whether session modality (in-person vs. video teleconference) affects outcomes by adding it as a level one predictor to all final models. We retain it as a control variable if it improves model fit. We will check the internal consistency of the threat prediction and outcome measures (other exposure measures are single item) using multilevel modeling [see (93)]. We will check the validity of exposure process measures by looking for expected patterns of associations among these variables (94).

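### The secondary model relates symptoms from baseline onward to exposure ratings first taken in session 5, without adjusting for pre-exposure symptoms, so its support rule can be met with no effect of prediction error

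*Protocol article*

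**What the plan says.** All references are to the protocol article.

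- **Aim.** Aim 2 in the Introduction expects that patients with more negative prediction error "will report fewer symptoms at the end of treatment and after 3 months". The Analysis section words the same hypothesis as improvement from baseline to 3-month follow-up.
- **Outcome.** "The outcome will be symptoms at 16 time points from baseline to 3-month follow-up".
- **Predictors.** For each participant, "we will calculate their mean P and O experienced across all exposures in treatment". This gives one txP and one txO per person.
- **Rule.** The hypothesis counts as supported if the interactions of assessment point with txP and with txO are both significant, with txP negative and txO positive.
- **Timing of symptoms.** Design: "Assessments will be made at baseline, before each session, mid-treatment, post-treatment, and 3-month follow-up".
- **Timing of exposures.** Exposure interventions: "Exposures begin from session 5 and are set for homework until the end of treatment". The section on ecological momentary assessment adds: "Participants complete their first survey and exposure during session 5, guided by their therapist".
- **Contrast with the primary model.** The primary analysis takes ratings from the preceding inter-session interval and controls for symptoms at the preceding session. Neither feature is stated for the secondary model.

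**The concern.** A predictor that is an average over sessions 5 to 12 is used to explain a trajectory that began before session 5. Part of the change it is said to predict has already happened when the first rating is made.

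This matters because ratings of threat partly reflect how ill the patient is. Suppose predictions still carry something of the patient's starting severity, while outcome ratings reflect the present state. The gap between prediction and outcome is then larger in patients who have already improved, for whatever reason. Treatment also includes psychoeducation and cognitive restructuring, so improvement need not come from exposure. The model would then return exactly the signs that the plan calls support. The claim at stake is whether average prediction error predicts treatment outcome.

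**Working it through.** **1. The plan's own count.** Baseline 1 + sessions 12 + mid-treatment 1 + post-treatment 1 + 3 months 1 = 16, as stated.

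**2. Order in time.** The session 5 score is taken before session 5, and the first exposure takes place during it. Baseline and sessions 1–5 therefore precede any rating: 1 + 5 = 6 of 16. At most three outcomes (session 12, post-treatment, 3 months) follow essentially all the exposures averaged into txP and txO.

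**3. Mechanism.** Let a be initial severity and s the mean severity over the exposure window. Write P = wP·a + (1 − wP)·s and O = wO·a + (1 − wO)·s, each plus noise. Then, apart from noise,

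P − O = (wP − wO)·(a − s).

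Here a − s is improvement already made. If wP > wO, the gap indexes that improvement. If wP = wO, it is noise only.

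**4. Null simulation of the planned rule.** From the plan: N = 65, 16 assessments, the support rule, and significance at 0.05 (given for the primary analysis; two-sided assumed). Assumed, because the documents give no values: baseline severity SD 1; mean change −1 with between-person SD 0.5 or 1.0; symptom error SD 0.5; rating error SD 0.4; linear assessment point. Exposures have zero effect on symptoms. Each person's slope over the 16 points was regressed on txP and txO, which for balanced data gives the same estimates as the interactions in a random-slope model. There were 4,000 runs per scenario. As a benchmark, if both true coefficients were zero, the rule could be met in at most 0.05/2 = 2.5% of runs, since each sign condition alone has that probability.

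Rule met (spread of change 0.5 / 1.0 SD):

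| Loadings on initial severity | All change before session 5 | Steady change |
|---|---|---|
| wP = 0, wO = 0 | 0.4% / 0.0% | 0.5% / 0.1% |
| wP = 0.5, wO = 0.5 | 0.6% / 0.4% | 1.2% / 0.6% |
| wP = 0.25, wO = 0 | 7.7% / 16.7% | 5.6% / 13.6% |
| wP = 0.5, wO = 0 | 32.2% / 83.8% | 22.2% / 73.6% |
| wP = 0.75, wO = 0 | 69.8% / 99.7% | 53.2% / 98.5% |
| wP = 1, wO = 0 | 90.4% / 100% | 78.0% / 100% |

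With no symptom change at all (wP = 1, wO = 0), the rule was met in 1.6% of runs.

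**5. Two alternatives under the same null.**

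- *Trajectory over only the 10 assessments after the first exposure.* The rule was met in 0.9–1.7% of runs when all change came before session 5. With steady change and wP > wO it was met in 3.5% to 98.4%.
- *Mean of post-treatment and 3-month symptoms, adjusted for baseline and the mean of the session 3–5 scores.* The rule was met in 0–5.4% of runs in every scenario but one. The exception was 31.1%, with steady change, wP = 1, wO = 0 and spread 1.0.

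**The case against.** Several points on the other side carry weight.

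- **Improvement from baseline needs baseline in the model.** The Analysis section does word the hypothesis that way, and a growth model describes it. This stands, so the analysis is not simply off target. But aim 2 in the Introduction is worded differently, and neither wording removes the time-order problem.
- **The aim is labelled exploratory and the study is described as correlational.** Both are true and limit the consequences. The exploratory label is given for reasons of power, however, and the plan still fixes a rule for support.
- **P and O use parallel items in the same survey.** Nothing in the article says that P carries more initial severity than O. This stands: with equal loading the rule is met in 0–1.2% of null runs.
- **The six early points are not the whole cause.** Steady change produces nearly as much false support as change confined to the early sessions. This stands, and it is why dropping the early points is not enough.

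A reader might also infer three stronger things that the article does not support. One is that the pre-exposure points carry about half the slope information. That is 167.5/340 = 49% with equally spaced linear coding, but 181/584 = 31% if weekly sessions are assumed, with mid-treatment at week 6.5, post-treatment at week 13 and follow-up at week 26. With categorical time no such share exists, and the coding is not stated. Another is that the step from post-treatment to 3 months is treated like one week, which rests on the same unstated coding. The third is that the sign condition is placed on the wrong terms. Its natural reading is the interactions.

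**Conclusion.** The concern holds in a conditional form. It is certain from the text that 6 of the 16 outcomes precede every predictor value and that no adjustment for pre-exposure symptoms is stated for this model. It is conditional that the rule misleads: it can be met without any effect of prediction error if P reflects initial severity more than O does and O reflects improvement already gained. Under that condition the null rate ran from about 6% to nearly 100%, depending on the loadings and the spread of change. All simulation parameters and the linear time coding are assumptions.

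A reader might conclude that false support is to be expected in this trial. The documents do not show that, because they give no information on how P and O load on severity. What can be said is that a positive result under the planned rule could not be told apart from improvement already under way. The consequence is confined to an exploratory secondary aim.

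**What to change.** Revise the secondary-analysis paragraph as follows.

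- Align the two wordings of the aim. Symptoms at the end of treatment and at 3 months, as in the Introduction, is the version that lets outcomes follow exposures.
- Regress post-treatment and 3-month symptoms on txP and txO, adjusting for baseline and the other pre-exposure assessments (the session 5 score and the mean of the earlier ones).
- Put the support rule on those coefficients: txP negative and txO positive, both significant.
- Report the results as associations. The adjusted model tested was similar to this one but not identical, and it reduced false support sharply without removing it in the most extreme scenario.

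Starting the trajectory at session 5 is not an adequate substitute, because the bias remains when change is steady over treatment.

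The cost is fewer outcome points and somewhat lower precision for an exploratory aim. No new data are needed.

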For in-session exposures, the therapist will prompt the participant to start a new survey just before doing the exposure. The therapist will ask the participant to read out each of their responses to the pre-experiment section so that the therapist is aware of their ratings and threat predictions. Once the pre-experiment section is complete, the therapist will prompt the participant to complete the planned activity and then the post-experiment section of the survey immediately after. The therapist asks the participant to read out their post-experiment survey responses and then reviews actual vs. predicted outcomes with the participant and what they learned from the activity. In this way, the EPQ also functions as a clinical tool for the therapist to elicit threat cognitions, structure the exposure, and conduct cognitive review afterward. A new survey is initiated for each new exposure attempted in a session. For between-session exposures, participants will be instructed to start a new survey immediately before every attempted behavioral experiment. Participants will be instructed to complete the post-experiment section as soon as possible after attempting these experiments. Accordingly, participants will work through their survey responses themselves without pre-post discussion *in situ* with their therapist.

The questionnaire measures the following exposure variables.

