#### Contextual features

In the pre-exposure section, participants type what social activity they plan to do and indicate whether they have attempted this activity before and if it is occurring in or between session. In the post-exposure section, participants indicate how soon after the exposure they are completing the questions, how long the exposure took, what the actual outcome of the exposure was, the type of location the exposure took place in, and the type of interaction partners present.

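### The tertiary surprise analysis pools therapist-guided and homework exposures with no term for setting, so the slope along the mismatch line is open to confounding; the curvature largely is not

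*Protocol article*

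**What the plan says.** The Analysis section gives the tertiary model in two parts. The data and outcome are: "We will use the EMA data without aggregation to perform multi-level RSA with surprise as the outcome". The right-hand side is "P and O and their higher order terms as predictors". The hypothesis, for either direction of error, is more surprise and a "greater likelihood for participants to report a learning outcome"; a model is written out for surprise only.

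One contextual covariate is named: "We will test whether session modality (in-person vs. video teleconference) affects outcomes by adding it as a level one predictor to all final models". It is kept only if fit improves.

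The section on the ecological momentary assessment (EMA) procedure describes two rating conditions:

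- **In session, before the exposure:** "The therapist will ask the participant to read out each of their responses to the pre-experiment section".
- **In session, after it:** "The therapist asks the participant to read out their post-experiment survey responses", followed by a joint review of predicted against actual outcome and of what was learned.
- **Homework:** "participants will work through their survey responses themselves without pre-post discussion" in the situation itself.

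Under Contextual features, participants state for each exposure "if it is occurring in or between session". No analysis in the article uses that answer.

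**The concern.** The two settings differ in who is present, in how the task is chosen and in whether the participant expects to report the ratings aloud. The Introduction itself suggests that unsupported homework exposures may mean more to the patient. Setting comes before P, O and surprise, so it could move the mismatch and, by a separate route, the surprise rating. It also varies within a person, so the person-mean centering planned in the Analysis section would not remove it.

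The in-person/video covariate does not do the job: an in-person client has both guided and homework exposures. The optional third level in the multilevel model concerns which therapist treats the client, not whether one is present.

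At stake is a construct-validity conclusion: whether self-reported P and O measure something that goes with surprise, and whether better-than-expected and worse-than-expected exposures behave alike. A setting effect shared by mismatch and surprise tilts the fitted surface along the mismatch line.

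**Working it through.** **1. How many records are in session.** From the section on exposure interventions: session 5 gives 1; session 6 is one activity done twice, so 1 or 2 records; session 7 gives 1; session 8 gives 1; session 9 gives 4. The total is 8 or 9 per completer. Two of the session 9 exposures are done individually, which leaves 6 or 7 done with the therapist. The article gives no homework count and says that it will vary, so the in-session share of all records cannot be derived.

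**2. Is there a figure to reproduce?** No. The only power statement (65 participants, 7 observations, standardized effect 0.18) concerns the primary analysis.

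**3. Simulation set-up (all assumed).** 65 people; 9 in-session and 5 to 20 homework exposures each. Person-level and residual SDs are 0.7 for P and surprise, so the total SD is √(0.49 + 0.49) = 0.99 and the shifts below are close to SD units. O = 0.3P plus its own person and residual terms (SD 0.7 each). P and O are person-mean centered and enter a second-order surface with coefficients b1 to b5 for P, O, P², PO and O². Neither P nor O affects surprise. Tested: slope b1 − b2 and curvature b3 − b4 + b5 along P = −O, with cluster-robust tests and 400 runs per scenario.

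**4. Slope along the mismatch line.** The shifts are those entered for in-session exposures. Because O carries 0.3P, the net O shift is 0.3 × (P shift) + (O shift).

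| P, O, surprise shift | Net gap shift | No setting term: mean slope, false rejection | With setting term |
|---|---|---|---|
| 0, 0, 0 | 0 | 0.002, 6.5% | 0.003, 4.75% |
| 0, 0, +0.4 | 0 | −0.004, 5.75% | 0.002, 6.25% |
| +0.3, −0.3, 0 | 0.51 | −0.001, 4% | 0.000, 6.75% |
| +0.2, −0.2, +0.2 | 0.34 | 0.043, 15% | 0.000, 5% |
| +0.3, −0.3, +0.4 | 0.51 | 0.124, 79% | 0.001, 6% |
| +0.5, −0.5, +0.5 | 0.85 | 0.227, 100% | 0.000, 4.5% |
| −0.3, −0.3, +0.4 | 0.09 | 0.016, 7.5% | −0.001, 5.75% |

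The bias needs both a gap shift and a surprise shift. With only one of them, or with almost no gap shift (last row), rejection stays at 4% to 7.5%.

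**5. Hand check of the 0.124.** The linear omitted-variable bias is b = (Σ + wδδ′)⁻¹ wδd, where Σ is the within-person covariance of P and O, δ their net shifts, d the surprise shift and w = π(1 − π).

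- π = 9/(9 + 12.5) = 0.419, so w = 0.243.
- δ = (0.30, 0.3 × 0.30 − 0.30) = (0.30, −0.21); d = 0.4.
- Σ: Var P = 0.49; Cov = 0.3 × 0.49 = 0.147; Var O = 0.09 × 0.49 + 0.49 = 0.534.
- Adding wδδ′: 0.512, 0.132 and 0.545. Right-hand side wδd: (0.0292, −0.0204).
- Solution: b1 = 0.071, b2 = −0.055; b1 − b2 = 0.126, against 0.124 simulated.

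**6. Curvature along the mismatch line, without the term.** Rejection was 5% to 9% in most scenarios. With shifts of ±0.5 and surprise +0.5 it was 14% with 0 to 5 homework exposures and 41% with 20 to 40.

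**7. A second set of assumptions.** With 9 in-session and 9 homework exposures each, false slopes occurred in 12% of runs (gap 0.5 SD, surprise 0.3 SD), 29% (0.5 and 0.5) and 63% (1 and 0.5), against 2% to 3% with the indicator. Curvature was not biased. Direction and remedy agree with step 4; the rates depend on what is assumed.

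**The case against.** The strongest reply is that the harm is hypothetical. Both shifts must exist and be direct, and the article gives neither. The direction is open too: an achievable session 5 task may lower P and shrink the gap. If guided exposures surprise more because they produce larger prediction error, that is the hypothesized effect and not confounding. In-session post-exposure ratings are entered straight after the activity and before the therapist's review, so only the expectation of reading them out could shape them. All of this stands, and it limits what can be said about size.

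Pooling is also deliberate: the Introduction criticizes earlier work for leaving out homework. That stands as well, but covering all exposures does not require ignoring their setting.

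A condensed article may leave covariates to a fuller plan. This carries less weight here, because the article lists the model's predictors and names one contextual covariate for all final models. The planned sensitivity test with time as a covariate may absorb a little of the difference, since guided exposures stop after session 9, but it is no substitute.

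Stronger readings that the document does not support:

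- **A false slope would lead to rejecting the either-direction hypothesis.** The Analysis section says only that surface parameters will be examined and states no such rule. The curvature mainly carries that hypothesis.
- **The learning analysis is biased in the same way.** No learning model is written out. The risk applies to whichever model is fitted to the same pooled records.
- **Guided exposures form a large share of the data.** The homework count is unknown.
- **The primary model needs the share of in-session exposures.** No bias was shown there, and that share partly tracks treatment time, for which the article explains its reluctance to adjust.

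**Conclusion.** The point holds as a gap in the model specification. The tertiary surprise surface pools two rating conditions, the variable separating them is collected, and no planned term uses it. The consequence is conditional: a biased slope along the mismatch line if being in session directly moves both mismatch and surprise. Under the assumed moderate shifts that bias is large enough to matter, and the setting term removes it. Neither the size nor the sign can be known from the document. The curvature is largely safe unless the shifts are large. Because the aim is tertiary and the either-direction hypothesis rests mainly on curvature, this is a worthwhile and cheap protection and does not threaten the main results.

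**What to change.** In the Analysis section's paragraph on the tertiary aim:

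1. Add the questionnaire's in-session/between-session item as a level-one predictor in the surprise model and in any model fitted for the learning outcome. Keep it whatever its effect on fit; the fit-based rule used for modality does not test for confounding.
2. Report the response surface for homework exposures alone as a sensitivity check.
3. State that the item is only a proxy for therapist presence, because two session 9 exposures are done individually.

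No change to the primary model is proposed.

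The cost is wording and one coefficient per model; no new data are needed. If setting has no direct effect on surprise, the term costs a little precision and introduces no bias. The homework-only surface is less precise. With 5 to 20 homework exposures beside 9 in-session ones (assumed counts), within-person information falls from 13 to 4 or from 28 to 19 degrees of freedom per person. Standard errors are then about √(13/4) = 1.8 to √(28/19) = 1.2 times as large. The Progress section reports 31 participants by January 2022 against a target of 65, so at that point the change could still be specified before analysis.
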